#### Data coding

Each participant will be assigned a screening number, and a trial randomisation number, allocated at randomisation, for use on trial documents and the electronic database. The documents and database will also use their initials and date of birth.

#### Status reports

The ATTACK database will produce status reports regularly and on request, including information on recruitment numbers, missing data, aspirin prescription and eGFR testing in trial participants.

#### Data storage and security

Case report forms (CRF) will be treated as confidential documents. The CRF will only collect the minimum required information for the purposes of the trial. CRFs will be held securely, in a locked room, or locked cupboard or cabinet. Access to the information will be limited to the trial staff and investigators and relevant regulatory authorities.

A separate confidential record of the participant’s name, date of birth, local hospital number or NHS number and Participant Trial Number (the Trial Recruitment Log) will be held securely on the trial database, to permit identification of all participants enrolled in the trial in accordance with regulatory requirements and for follow-up as required.

Computer-held data including the trial database will be held securely and password protected. All data will be stored on a secure dedicated web server within the NHS Private Data Network, to which only authorised study personnel will have access. This is compatible with and has the relevant security policies in place, to obtain patient-matched hospital admission data and ONS data for consented patients from NHS Digital. Access will be restricted by user identifiers and passwords (encrypted using AES-25S encryption). Electronic data will be backed up every 24 h to both local and remote media in encrypted format.

#### Data retention

In adherence with the International Conference on Harmonisation (ICH) Good Clinical Practice (GCP) guidelines, the Chief or local Principal Investigator will maintain all records and documents regarding the conduct of the study. These will be retained for up to 10 years after the date of any publication based on the research data. If the responsible Investigator is no longer able to maintain the study records, a second person will be nominated to take over this responsibility. The Trial Master File and trial documents held by the Chief Investigator on behalf of the Sponsor shall be finally archived at secure archive facilities at the Sponsor site. This archive shall include all trial databases and associated metadata encryption codes. This will all be in accordance with the Sponsor’s Standard Operating Procedures (SOP).

### Statistical methods

Analyses will be intention-to-treat (ITT), consisting of all patients who have consented and have been randomised to a treatment arm.

For the primary outcome measure (composite of non-fatal myocardial infarction, non-fatal stroke and cardiovascular death [excluding confirmed intracranial haemorrhage and other fatal cardiovascular haemorrhage]), deaths from other causes (including fatal bleeding) will be treated as competing events. Patients who do not experience a major vascular event will be censored at the date of last follow-up.

As non-fatal major bleeding and anticoagulation are events, which, in the intervention arm, may lead to aspirin cessation, sensitivity analyses of the primary outcome measure (for the ITT population) will also include:
Censoring patients who experience non-fatal major bleeding (adjudicated), clinically relevant non-major bleeding, or anticoagulation at the date of the event (whichever occurs first)Censoring only patients who experience non-fatal major bleeding (adjudicated) at the date of the event

For the secondary outcomes of time to fatal/non-fatal major haemorrhage (both intracranial and extracranial), the following competing risk models will be used to assess impact of assumptions over competing risk and censoring:
Deaths from other causes (excluding fatal bleeding) will be treated as competing events. Patients who experience a major vascular event will be censored at the date of the event. Patients who do not experience either a major vascular event or fatal/non-fatal major event will be censored at the date of last follow-upMajor vascular events and deaths from other causes (excluding fatal bleeding) will be treated as competing events. Patients who do not experience a fatal/non-fatal major vascular event will be censored at the date of last follow-upMajor vascular events and deaths from other causes (excluding fatal bleeding) will be treated as competing events. Patients who experience anticoagulation or clinically relevant non-major bleeding will be censored at the date of the event (whichever occurs first). Patients who do not experience either anticoagulation, clinically relevant non-major bleeding, or a fatal/non-fatal major vascular event will be censored at the date of last follow-upDeaths from other causes (excluding fatal bleeding) will be treated as competing events. Patients who experience anticoagulation, clinically relevant non-major bleeding, or a major vascular event will be censored at the date of the event (whichever occurs first). Patients who do not experience either anticoagulation, clinically relevant non-major bleeding, a major vascular event or a fatal/non-fatal major event will be censored at the date of last follow-up

Time to event data will be described using Kaplan-Meier curves (or Cumulative Incidence curves for time to event outcomes involving competing risks). Analyses of time to event outcomes will be performed using a Cox proportional hazards model (or Fine and Gray’s adaptation of the Cox proportional hazards model for the subdistribution of a competing risk [87], i.e. a Competing Risk regression model for time to event outcomes involving competing risks), both unadjusted and adjusted for stratification factors: age, diabetes and CKD severity. The proportional hazards assumption will be assessed graphically with a log-log plot and a Schoenfeld test based on scaled Schoenfeld residuals.

The adjusted competing risk regression model for time to first major vascular event, with deaths from other causes (including fatal bleeding) treated as competing events, and patients who do not experience a major vascular event censored at the date of last follow-up, will form the primary endpoint analysis model.

Negative binomial regression will be used to analyse unplanned hospitalisations, both unadjusted and adjusted for stratification factors: age, diabetes and CKD severity.

For other secondary and tertiary endpoints, we will compare proportions for categorical data and means/medians for continuous data using Pearson’s *χ*^2^ test and *T* test/Mann-Whitney *U* test, respectively.

The amount of missing data and reasons for the incompleteness will be explored and presented overall, i.e. not by group. If the amount of missing data is deemed too high and if appropriate (i.e. assuming the missing data is either missing at random or missing completely at random and censoring assumed to be non-informative), multiple imputation will be performed accordingly, for which all covariates included in the multivariable model, together with the censoring/event indicator and the cumulative baseline hazard will be included in the multiple imputation model.

All statistical analyses will be carried out using Stata v15 or higher, or SAS v9.4 or higher.

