#### Secondary endpoints

The secondary endpoints will be analysed as time to event from date of randomisation through to the end of follow-up with the exception of health-related quality of life (HRQoL). HRQoL will be measured using annual EQ-5D-5L questionnaires [63] and converted to utilities. Cost utility analysis will be performed to determine incremental costs and health improvements expressed in the unit of quality adjusted life years.
(i)EfficacyDeath from any causeComposite outcome of major vascular event or revascularisation (coronary and non-coronary)Individual components of the primary composite endpointHealth-related quality of life(ii)SafetyComposite outcome of intracranial haemorrhage (fatal and non-fatal), fatal extracranial haemorrhage and non-fatal major extracranial haemorrhage (adjudicated)Fatal and non-fatal (reported individually and as a composite) intracranial haemorrhage comprising:
Primary haemorrhagic stroke (to distinguish from haemorrhagic transformation of ischaemic stroke): (i) intracerebral and (ii) subarachnoid haemorrhage (reported individually and a composite) (adjudicated)Other intracranial haemorrhage: (i) subdural and (ii) extradural haemorrhage (reported as a composite) (adjudicated)Intracranial haemorrhage will be subcategorised as traumatic or non-traumatic [64]Fatal and non-fatal (reported individually and as a composite) major extracranial haemorrhage: (i) upper gastrointestinal; (ii) lower gastrointestinal; (iii) sight-threatening ocular; (iv) multiple trauma; (v) other (adjudicated)Clinically relevant non-major bleeding (if hospitalised) (adjudicated)Composite outcome of fatal and non-fatal major extracranial haemorrhage and clinically relevant non-major bleeding (if hospitalised)

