#### Tertiary endpoints

Exploratory endpoints will be analysed as time to event from the date of randomisation through to the end of follow-up except hospitalisations, which will be reported as a rate over time.
Transient ischaemic attackUnplanned (emergency) hospitalisationsHospitalisation with heart failureNew diagnosis of cancer (colorectal/other)Death due to cancer (where cancer is the underlying cause of death)CKD progression (at least one of: > 30% fall in eGFR over 2 years [65]; need for renal replacement therapy or 50% decline in eGFR [66]; new eGFR< 15 mL/min/1.73 m^2^; 25% decline in GFR together with a drop in GFR category [3])New diagnosis of dementiaMajor non-traumatic lower limb amputation

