#### Consent consultation

Potential participants who respond to express an interest will be contacted, primarily by telephone, to give them further information and allow them to ask questions. Suitable patients will be invited to a consent consultation.

In the light of the 2020 Coronavirus pandemic, a decision was taken in Summer 2020 to offer remote consultations. No screening tests will now be taken; instead, laboratory-based checks of eligibility will be based on pre-existing blood and urine test results available within the GP electronic patient record (EPR). The effect of this is to render the trial entirely Covid-secure, as no face-to-face assessment are required at any stage in the trial. This is important as CKD is a risk factor for poor outcomes in Covid-19 [74]. Prior to this, potentially eligible patients in ATTACK underwent screening eGFR and UACR testing at a face-to-face screening visit to confirm eligibility.

During the virtual consent consultation, inclusion and exclusion criteria will be checked and the patient consented by an appropriately trained research nurse or registered medical professional with suitable study training. If the consenting individual has any concerns over the eligibility of a patient, they will discuss it with the GP at the practice, who will ultimately decide if the patient is suitable.

Latest blood pressure will be extracted from the EPR. Basic demographic and clinical details will be recorded at consent, including self-defined ethnicity, height and weight, smoking history, and alcohol consumption. All participants will also complete an EQ-5D-5L questionnaire.

Additional information, including postcode (used to generate Index of Multiple Deprivation), summary diagnoses, cardiovascular risk factors (for example diabetes [type and duration], hypertension and lipid profile) and concomitant medications will also be automatically extracted from the EPR as required.

The GFR category at entry will be determined according to the most recent CKD-EPI eGFR, currently corrected for ethnicity. For sites where the Modification of Diet in Renal Disease (MDRD) eGFR is reported, CKD-EPI eGFR will be calculated from the standardised serum creatinine. The inclusion of correction factors for ethnicity has been reassessed by the American Society of Nephrology and National Kidney Foundation [75], and we have adopted the recommendations from NICE in August 2021 to remove these [76].

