#### Participant retention

The use of routinely collected hospital, GP and national mortality and cancer data will allow a full ITT analysis on all participants who are randomised, including those who discontinue study treatment as a result of a clinical decision, non-compliance with the Protocol or drug toxicity, with the exception of those who withdraw from the study. Withdrawal is defined as the withdrawal of consent for record linkage and the collection of follow-up data. We are assuming a 1% dropout rate according to this definition as we are expecting almost complete linkage of the trial participants to national data on hospitalisation (HES), deaths and new cancers (ONS) which will enable event capture and adjudication. Subjects will be free to withdraw from the trial at any time and will be informed that should they withdraw data collected prior to withdrawal may be used in the final analysis if they agree at this time. Subjects will be contacted annually and thanked for their valuable contribution to the study.

Subjects who do not participate in annual follow-up for EQ-5D-5L and self-reported health events and health service contacts will still be followed up for major outcomes.

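### Health-related quality of life is left to a two-sample test that uses neither the baseline EQ-5D-5L, nor the annual repeats, nor the stratification factors

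*Protocol article*

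**What the plan says.** HRQoL is a listed secondary efficacy endpoint. The Secondary endpoints section analyses the secondary endpoints as time to event "from date of randomisation through to the end of follow-up with the exception of health-related quality of life (HRQoL"). It adds that "HRQoL will be measured using annual EQ-5D-5L questionnaires" and that the scores are converted to utilities. A baseline value exists too: under Consent consultation, "All participants will also complete an EQ-5D-5L questionnaire", and randomisation follows only after consent is complete.

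The Tertiary endpoints section reads: "Exploratory endpoints will be analysed as time to event from the date of randomisation through to the end of follow-up except hospitalisations", which are reported as a rate.

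Statistical methods gives Cox or Fine and Gray models for time-to-event outcomes, each run unadjusted and adjusted for the three stratification factors. It continues: "Negative binomial regression will be used to analyse unplanned hospitalisations, both unadjusted and adjusted for stratification factors: age, diabetes and CKD severity". Then comes the residual rule: "For other secondary and tertiary endpoints, we will compare proportions for categorical data and means/medians for continuous data using" Pearson's chi-squared test for the former and a t-test or Mann-Whitney U test for the latter.

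On missing data, Participant retention states: "Subjects who do not participate in annual follow-up for EQ-5D-5L and self-reported health events and health service contacts will still be followed up"; the follow-up meant is that for major outcomes. Statistical methods allows multiple imputation if missingness is judged too high and if it is appropriate. The model covariates, "together with the censoring/event indicator and the cumulative baseline hazard will be included in the multiple imputation model". The amount of missing data and the reasons are to be shown overall and not by arm.

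**The concern.** An outcome measured before randomisation and every year afterwards is normally analysed with its baseline as a covariate and with all visits in one model. The stated rule does neither. It also leaves HRQoL as the one listed endpoint without an analysis adjusted for the stratification factors, although these were built into the randomisation and are used everywhere else.

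What is at stake is mainly precision. Information that patients have already supplied is not used, so the interval for the utility difference is wider than it need be.

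A second, conditional issue is robustness. Routine records secure follow-up for clinical events but do not contain EQ-5D-5L, so HRQoL depends on patients replying. Patients know their allocation. If reply depended on baseline HRQoL differently in the two arms, an unadjusted comparison of responders would be biased, while one adjusted for baseline would not be biased by that mechanism.

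**Working it through.** **Step 1. Which endpoints fall under the residual rule?**

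- Secondary endpoints: all time to event except HRQoL.
- Tertiary endpoints: time to event except hospitalisations, which are a rate; unplanned hospitalisations get negative binomial regression.
- Listed continuous endpoint with no other method: HRQoL only.

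**Step 2. The plan's own figures.** None is given for HRQoL. The sample size of 12,605 per arm belongs to the primary endpoint. With 85% power and two-sided 5%, events = 4 × (1.960 + 1.036)² / ln(0.8692)² gives 1828 (stated 1827). 1827/0.0732 = 24,959 (stated 24,958), and dividing by 0.99 gives 25,211 (stated 25,210). These figures reproduce, and nothing below changes them.

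**Step 3. Gain from baseline adjustment at one visit.** The article gives no correlation r between baseline and follow-up utility, so 0.5 to 0.7 is assumed. Relative to the t-test, the variance factor is 1 − r², the interval-width factor is √(1 − r²), and the equivalent number of respondents is 1/(1 − r²).

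| r | Variance factor | Variance cut | Width factor | Width cut | Equivalent n |
|---|---|---|---|---|---|
| 0.5 | 0.75 | 25% | 0.87 | 13% | 1.33 |
| 0.6 | 0.64 | 36% | 0.80 | 20% | 1.56 |
| 0.7 | 0.51 | 49% | 0.71 | 29% | 1.96 |

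**Step 4. Gain from using the repeats as well.** For the average of k visits under compound symmetry with complete data, the variance factor is (1 + (k − 1)r)/k − r². With k = 3 and r = 0.6 this is 2.2/3 − 0.36 = 0.37. At r = 0.5 it is 0.42, and at r = 0.7 it is 0.31. The target here is the average over visits, not the value at one visit.

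**Step 5. Does precision matter at this size?** The t-test's detectable difference at 85% power is (1.960 + 1.036) × SD × √(2/n). Assumptions: SD 0.20 to 0.30, response 50 to 90%, and 10% lost to death, so n = 12,605 × response × 0.9.

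- SD 0.20, response 90%: n = 10,210, difference 0.008.
- SD 0.30, response 50%: n = 5,672, difference 0.017.

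With r = 0.6 and baseline adjustment these fall to 0.007 and 0.014. The plain test already detects small differences.

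**Step 6. Response that depends on baseline HRQoL.** An illustrative simulation used 12,605 per arm, no true effect, r = 0.6, about 70% response and 200 replicates. The Monte Carlo error of a 5% rate is √(0.05 × 0.95/200), about 1.5 points. The slopes are the assumed logit slopes of response on baseline in usual care and aspirin.

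| Slopes | t-test bias (SD) | t-test false positives | Baseline-adjusted false positives |
|---|---|---|---|
| 0.5, 0.5 | 0.000 | 7% | 6% |
| 0.5, 0.4 | −0.018 | 23.5% | 5% |
| 0.5, 0.25 | −0.045 | 81% | 8.5% |

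The adjusted estimate was essentially unbiased throughout (at most 0.001 SD). That is partly by construction, since response depended on baseline alone.

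**Step 7. Deaths.** Inputs from the sample size section: other-cause death 1.8% and 1.85% a year, primary events 2% a year, HR 0.868. Cardiovascular deaths are taken as 1/2.8 of primary events, from the quoted 1.8:1 ratio of non-fatal to fatal events. At 4.25 years (2.5 + 3.5/2, mean follow-up under uniform accrual):

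- Usual care: 1 − exp(−(0.01816 + 0.00722) × 4.25) = 10.2%, about 1,290 of 12,605.
- Aspirin: 1 − exp(−(0.01867 + 0.868 × 0.00722) × 4.25) = 10.1%, about 1,270.

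The arms are nearly equal. Deaths therefore raise the question of what the comparison describes (utility in survivors) more than one of imbalance.

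**The case against.** The strongest reply is that the sentence never mentions HRQoL. The same elimination leaves no listed endpoint for the chi-squared test, so it may be a generic catch-all. That is fair, and the link to HRQoL is an inference. It is still the only between-arm analysis the article offers for this endpoint.

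A second reply is that the article condenses a longer plan. The HRQoL time point, the summary contrast and the rule for deaths commonly sit in the analysis plan, so their absence is no finding. That stands. The point rests on the test that is stated.

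A third is that precision is not the limit with 12,605 per arm. That also stands (Step 5), and the t-test interval is valid, only less efficient.

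Several stronger readings are tempting but unsupported:

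- That missing questionnaires are simply mishandled. The article has a conditional imputation clause. Its listed ingredients suit survival models, but nothing bars its use for HRQoL.
- That differential response has been shown. No response rate is given, the slopes in Step 6 are invented, and with equal dependence in both arms the t-test is unbiased.
- That yearly testing creates a multiplicity problem. The article proposes no separate yearly tests.
- That the QALYs are compromised. Health economic analysis takes utilities from its own regression and treatment effects from the Cox or competing-risk models. The t-test result does not enter.

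**Conclusion.** The point holds as a concrete, nearly free improvement to one secondary endpoint. By elimination, the stated method for HRQoL is a two-sample test that leaves the baseline, the annual repeats and the stratification factors unused. At an assumed correlation of 0.5 to 0.7, baseline adjustment alone reduces the variance by 25 to 49% and the interval width by 13 to 29%. Under compound symmetry, using three annual visits as well brings the variance factor to 0.42 to 0.31. The documents supply no SD, correlation or response rate, so these sizes are illustrative.

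The robustness argument is conditional: adjustment protects against arm-specific response that depends on baseline, a pattern that an open-label design allows but the documents do not demonstrate. A reader might infer that the HRQoL result would be wrong as planned. The documents support only that it would be less precise and less protected. The primary analysis, the sample size and the economic model are untouched.

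**What to change.** For EQ-5D-5L utility, replace the two-sample test with a linear mixed model for repeated measures:

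- covariates: baseline utility, age, diabetes and CKD severity;
- arm, year and arm-by-year terms, using all annual visits;
- one contrast named in advance, for example the arm difference averaged over follow-up.

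Report questionnaire missingness by arm as well as overall. Add a sensitivity analysis that includes deaths, for example with utility set to 0 after death. This is needed because the mixed model treats values after death as missing. Scoring death as 0 is one convention among several, so state it in advance. The model will not remove bias if reply depends on current, unobserved HRQoL, which is a further reason to show missingness by arm.

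The cost is a change of wording and modest programming. No extra data, visits or patients are needed.

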### Health economic analysis

Economic analysis will follow the methods and “reference case” recommended by NICE [88]. Modelling will be used to estimate the net effect of aspirin prescribing on healthcare costs and quality-adjusted survival over a lifetime horizon, using trial data to estimate effects on vascular and bleeding risks, cancer incidence, CKD progression and mortality. Trial data will also be used to estimate health-related quality of life and healthcare costs for the population and associated with adverse events.

Costs will be estimated using individual-level linked HES/GP data, supplemented where necessary with information from the patient questionnaire. Costs will be estimated for services potentially affected by aspirin use, including prescriptions (aspirin, gastroprotective and other related drugs); primary care consultations; unplanned admissions for bleeds and vascular events, with related follow-up (e.g. revascularisations); renal replacement therapy following CKD progression.

Unit costs for services will be obtained from standard national sources: NHS Reference Costs for admissions and other hospital services; Personal Social Services Research Unit estimates for primary care and community services; and British National Formulary/Drug Tariff for drug prices.

Quality-adjusted life years (QALYs) will be estimated using data on survival and quality of life (EQ-5D-5L) questionnaires. EQ-5D-5L scores (“utilities”) will be calculated using a UK general population value set, as recommended by NICE at the time of analysis [89, 90]. Costs and QALYs will be discounted at NICE recommended rates (currently 3.5% per year for both).

The model structure, parameter sources and methods of analysis will be specified in a detailed economic protocol paper, informed by a review of high-quality CKD and CVD prevention models. We expect to use an individual-level discrete-event simulation approach to reflect the multiple, competing risks of vascular, haemorrhagic and other related events in this population over a lifetime horizon, taking advantage of the large pragmatic trial dataset [91]. Distributions of baseline characteristics and risk factors will be estimated from trial data. Control arm data will be used to characterise event rates under usual care: e.g. using Cox proportional hazards predictive equations for CVD events and CKD progression; and parametric survival models (e.g. Gompertz) for all-cause survival (pre- and post-event, and by CKD stage or severity) [92]. Relative treatment effects will be taken from the main trial analyses described above under "Statistical methods" (Cox proportional hazards or competing hazards regressions). The impact of events on patients’ quality of life (EQ-5D-5L utility scores) and NHS costs will be estimated from trial data by an appropriate regression approach [93]. If an effect on cancer incidence is found, this will be included in the economic model, although we may need to source background risk, cost and utility parameters for this outcome from the literature.

Uncertainty over model results will be explored through sensitivity analysis. Deterministic analysis will be used to investigate the sensitivity of results to input parameters and key modelling assumptions. Probabilistic analysis will be used to assess the extent and impact of uncertainty over model inputs. Results will be stratified by pre-defined subgroups and CVD risk.

Validity of the model will be assessed by a Health Economist not involved in its development. This will include tests of internal validity: checks that input parameters match specified sources and inspection of coding (white box validation), stress testing of model behaviour (black box validation) and comparison of modelled event rates during the trial follow-up period with trial observations. External validity will be assessed by comparison of intermediate model results (event rates) with relevant estimates from the literature (identified by systematic review).

